## Abstract

**Background:**

Cardiovascular diseases (CVD) are cause of increased morbidity and mortality in spite of advances for diagnosis and treatment. Changes during pregnancy affect importantly the maternal CV system. Pregnant women that develop preeclampsia (PE) have higher risk (up to 4 times) of clinical CVD in the short- and long-term. Predominance of an anti-angiogenic environment during pregnancy is known as main cause of PE, but its relationship with CV complications is still under research. We hypothesize that angiogenic factors are associated to maternal cardiac dysfunction/remodeling and that these may be detected by new cardiac biomarkers and maternal echocardiography.

**Methods:**

Prospective cohort study of pregnant women with high-risk of PE in first trimester screening, established diagnosis of PE during gestation, and healthy pregnant women (total intended sample size *n* = 440). Placental biochemical and biophysical cardiovascular markers will be assessed in the first and third trimesters of pregnancy, along with maternal echocardiographic parameters. Fetal cardiac function at third trimester of pregnancy will be also evaluated and correlated with maternal variables. Maternal cardiac function assessment will be determined 12 months after delivery, and correlation with CV and PE risk variables obtained during pregnancy will be evaluated.

**Discussion:**

The study will contribute to characterize the relationship between anti-angiogenic environment and maternal CV dysfunction/remodeling, during and after pregnancy, as well as its impact on future CVD risk in patients with PE. The ultimate goal is to improve CV health of women with high-risk or previous PE, and thus, reduce the burden of the disease.

**Trial registration:**

NCT04162236

## Background

Cardiovascular diseases (CVD) are cause of increased morbidity and mortality in spite of advances for diagnosis and treatment. Manifestations of CVD, risk factors and treatment are different in women than in men; women are affected by traditional CVD risk factors, but also by gender-specific ones, such as polycystic ovarian syndrome or pregnancy-associated disorders such as preeclampsia (PE) [1]. In 2011, the American Heart Association (AHA) guideline for preventing CVD in women included PE, gestational hypertension, diabetes mellitus, and systemic autoimmune collagen-vascular disease (i.e., lupus or rheumatoid arthritis) as factors associated with increased risk of CVD [2]. Later, in 2018 and 2019, the AHA/ACC Multisociety Guideline on the Management of Blood Cholesterol [3]; and the American College of Cardiology (ACC)/AHA guidelines [4] introduced the concept of women-specific factors to consider for risk, diagnosis and treatment of CVD; these factors now included PE.

One of the most prevalent complications of pregnancy is PE. Epidemiological studies have shown that PE is associated with development of CV risk factors, hypertension, myocardial infarction, stroke, renal complications, vascular and metabolic dysfunction during pregnancy and in later years. Pregnant women that develop preeclampsia (PE) have higher risk (up to 4 times) of clinical CVD in the short- and long-term [5, 6]. When PE is accompanied by preterm birth and/or small for gestational age, the adjusted risk for CVD is increased by 45% for the next 5 years post-partum [7]; risk comparable to that of smoking. Therefore, as history of PE has recently been incorporated by the aforementioned societies as an independent risk factor for CVD [8], follow-up starting within the fourth decade of life is recommended by some authors [9]. All these facts highlight the need to prevent and diagnose PE during pregnancy, and follow-up these women after delivery.

Changes during pregnancy affect importantly the maternal CV system, in order to maintain adequate fetal blood perfusion; maternal cardiac output and heart rate increase, while blood pressure and vascular resistances decrease [10]. In PE, CV adaptation in pregnancy is abnormal, exceeding physiological levels, which occurs more frequently if there is a hypertensive disorder before pregnancy. In fact, CV findings in PE resemble those due to cardiac diastolic dysfunction; i.e., improper left ventricle (LV) relaxation, increased LV chamber stiffness, and increased cardiac filling pressures [11], all of which can be detected by echocardiography.

PE is also characterized by endothelial dysfunction, which results from an imbalance between maternal circulating angiogenic factors, like pro-angiogenic placental growth factor (PlGF), and anti-angiogenic factors such as soluble fms-like tyrosine kinase 1 (sFlt-1) [12]. Placental expression and maternal circulating concentrations of sFlt-1 are increased in PE [13], whereas PlGF is decreased. This occurs due to a combination of decreased expression because of poor placentation, and reduced free PlGF due to sFlt-1 binding [14]. This leads to an increase in the sFlt-1/PlGF ratio, which has been described as better predictor for PE severity than either marker alone [15]. Recently, our group reported an association between angiogenic factors during pregnancy and CV disease 12 years post-partum, suggesting angiogenic factors are important players in PE-associated CV risk later in life [16].

In addition to maternal CV effects, fetal cardiac programming during pregnancy and its relationship with angiogenic environment has not been previously assessed. Fetal programming refers to the impact on fetal health due to intrauterine environment [17]. It occurs when the fetal environment is modified by an adverse condition in a critical moment of development. Pregnancy complications such as PE and intrauterine growth restriction are associated with fetal programming [18, 19]. However, little is known on the role of angiogenic biomarkers for early detection of fetal cardiac abnormalities and programming in PE pregnancies.

Multiple biomarkers have been assessed to evaluate CVD risk or myocardial damage in PE. Arginine vasopressin (AVP) has been shown to reproduce main maternal and fetal PE features in animal models [20] and some studies propose its more stable metabolite, copeptin, as an early predictor of PE [21]. Thus, AVP concentration is estimated measuring copeptin. Cardiac troponins (cTn) are isoforms solely produced by myocardial cells. When measured by high-sensitivity (hs) methods, cTn can detect small amounts released in myocardial ischemia. Few studies have analyzed hs-cTn in PE [22]; thus, it remains to be determined whether hs-cTn could detect minor myocardial damage in PE women. Natriuretic peptides are biomarkers of cardiac volume overload, vascular hypertension and myocardial elongation. All these conditions are observed in PE, and particularly those of the B-family (B-type natriuretic peptide, BNP), have been analyzed in normal and hypertensive pregnancies and found to be biomarkers for CV alterations in PE [23]. BNP is synthetized as a prehormone (pro-BNP), which is cleaved to an N-terminal fragment (NT-proBNP), and both are associated with hemodynamic stress and heart failure.

We hypothesize that an association exists between the anti-angiogenic environment and cardiac dysfunction/remodeling in women at risk for PE during pregnancy and their offspring, and that this relationship could determine an increased CV risk later in life.

## Aims

### Primary aim

To determine if a relationship exists between angiogenic environment during pregnancy and the risk of maternal cardiovascular dysfunction and remodeling.

### Secondary aims

To prospectively assess both biochemical and biophysical CV markers in a cohort of patients with risk for PE and in healthy pregnant women, in the first and third trimesters of pregnancy.To determine correlation between angiogenic (PlGF) and anti-angiogenic (sFlt-1) factors in maternal serum, and biochemical and imaging markers of cardiac dysfunction and remodeling in patients with established PE.To evaluate the relationship between placental and maternal cardiac biomarkers and fetal cardiac function in the third trimester of pregnancy.To determine cardiac dysfunction and metabolic status 12 months after delivery in women with PE, and its correlation with CV and PE risk variables obtained during pregnancy.To investigate angiogenesis and CV-related genes in placental samples of women with PE and controls, by microarray and polymerase chain reaction (PCR) validation.To develop a combined model for prediction of cardiovascular risk in PE, that includes placental and cardiac biomarkers, clinical and echocardiographic variables.

## Methods

### Trial registration

https://clinicaltrials.gov/NCT04162236
.

### Study design

Prospective cohort study which will include the following patients: pregnant women with high-risk of PE in first trimester screening, established diagnosis of PE during gestation, and healthy pregnant women (controls).

### Setting/location

Santa Creu i Sant Pau University Hospital, Universitat Autònoma de Barcelona, Barcelona, Spain.

### Inclusion criteria

Women between 18 and 45 years of age, with singleton pregnancies and high-risk for PE according to our first trimester screening protocol [24], which includes registration/measurement of maternal risk factors, blood pressure (BP), pregnancy-associated plasma protein A (PAPP-A) and mean uterine artery pulsatility index (UtA-PI), at 11^+ 0^ to 13^+ 6^ weeks of gestation. The estimated sample size for the high-risk group is 280 patients, who will be divided according to the subsequent development of PE:True PE: women from the high-risk group who develop PE (estimated *n* = 40)False PE: women from the high-risk group who do not develop PE (estimated *n* = 240)

An additional group of healthy pregnant women with first trimester low-risk screening for PE will be recruited (*n* = 100).

Additionally, women with established diagnosis of PE (*n* = 60) that were not participating previously in the study, will be included at time of diagnosis. The local research coordinator and/or staff will identify eligible women, invite them to participate, provide written and oral information, and obtain the written informed consent.

### Exclusion criteria

Pregnancies with previous maternal conditions such as thrombophilia, type-1 diabetes, hyperthyroidism, any renal disease, severe maternal illness, cytomegalovirus or toxoplasmosis infection, maternal human immunodeficiency virus infection, previous venous or arterial thrombotic events, alcohol or illicit drug use, as well as multiple pregnancies, major fetal anomaly or chromosomal anomalies.

### Procedures and interventions

Patients will be invited to participate after first trimester screening (11-13^+ 6^ weeks); once they have consented to the study, a maternal echocardiographic evaluation will be performed, and blood and urine samples will be obtained. Patients will be scheduled at third trimester (28-32 weeks of pregnancy) for a second maternal echocardiographic evaluation, a fetal functional echocardiographic evaluation and a second blood sample. If a patient develops PE before the scheduled evaluations, all studies will be conducted before delivery. At birth, umbilical cord blood, maternal blood and placental samples will be obtained for evaluation of biomarkers. Finally, a maternal echocardiographic evaluation will be scheduled 12 months after delivery, with final blood and urine samples for biomarker analysis. Figure 1 shows the timeline for the planned interventions.

**Fig. 1 Fig1:**
[figure not shown]
Timeline of the planned interventions: ANGIOCOR study. PE, preeclampsia; CV, cardiovascular; BP, blood pressure; UtA-PI, uterine artery pulsatility index

#### Maternal echocardiography

Maternal echocardiographic evaluation will be performed at first trimester, 28-32 weeks’ gestation and 12 months postpartum, by a Cardiologist specialized in cardiac imaging, according to the usual standard protocol [25]. High-resolution images will be acquired with Affinity 70G (Philips, Andover, MA, USA) ultrasound machine, with post-processing analysis with a dedicated cardiovascular software, including myocardial strain analysis by 2D speckle-tracking (Philips AutoStrain LV). The following parameters will be evaluated: LV dimensions (end-diastolic diameter (EDD), end-systolic diameter (ESD), end-diastolic volume (EDV), end-systolic volume (ESV)) and thickness (interventricular septum (IVS) and posterior wall (PW)), left ventricular ejection fraction (EF) obtained by Teicholz and Simpson methods, LV myocardial deformation (strain) parameters, cardiac output, left atrial volume, Doppler transmitral flow analysis including tissue Doppler imaging (TDI) and right heart evaluation including ventricular diameters, tricuspid annular ring systolic excursion (TAPSE) and TDI of the tricuspid lateral annulus.

#### Fetal echocardiography

Fetal echocardiographic examination will be performed at 3rd trimester of gestation according to the International Society of Ultrasound in Obstetrics and Gynecology guideline [26]. Briefly, cardiac axis and situs, pericardial effusions, ventricular morphology, veno-atrial, atrioventricular and ventricle-arterial connections, size and relationships of left and right ventricular outflow tracts, ductal and aortic arches, atrial size, interventricular septum (IVS) and flow through atrioventricular (AV) and semilunar valves will be evaluated using two-dimensional, color and pulsed Doppler ultrasound. Fetal functional echocardiography will include the following parameters according to published methodology [27]: in the 4-chamber view EDD, ESD, IVS, myocardial wall thicknesses in diastole (calculation of SF and EF for each ventricle) and cardiothoracic ratio. With pulsed Doppler: early and late peaks of transvalvular filling velocities of left and right ventricles (E/A ratio calculation) [28], aortic valve and pulmonary valve peak systolic velocities, velocity time integrals, and fetal heart rate will be measured, and valve diameters will be acquired in 2D for calculation of cardiac outputs. With M-mode: mitral annular-plane systolic excursion (MAPSE) and TAPSE [29]. Finally, left isovolumetric contraction and relaxation times, and ejection time will be measured for calculation of myocardial performance index, as previously described [30].

#### Biomarker analyses

All blood samples will be collected without anticoagulants. Biomarkers sFlt-1, PlGF, hs-cTnT and NT-proBNP will be measured using automated electrochemiluminescence immunoassays on a Cobas E601 platform (Roche Diagnostics GmbH, Mannheim, Germany). Copeptin will be measured in a KRYPTOR lab instrument by an immunoluminometric assay using two polyclonal antibodies (BRAHMS, Thermo-Fischer, Germany )[21]. The clinical laboratory involved in the study performs standard internal and external quality controls for biomarkers included in the study. For interpreting observed values we will use reference values or ranges obtained in previous studies or recommended guidelines.

#### Ambulatory blood pressure monitoring (ABPM)

Blood pressure (BP) measurements will be carried out by a 24-h monitoring with the ABPM 7100 (Welch Allyn, Skaneateles, NY, US) that measures brachial or peripheral BP and central BP, in addition to pulse wave velocity. Peripheral BP will be monitored every 20 min and central BP every 60 min throughout the 24-h period. Day and night periods will be defined according to waking and sleeping periods reported by patients. Peripheral and central BP monitoring will register systolic, diastolic and mean BP during day- and night-time periods and the night/day ratio of the different measurements; peripheral measurements will also include heart rate and pulse wave velocity.

### Data collection

Patients and healthy controls will be asked to complete a questionnaire including demographic, anthropometric, personal and familiar clinical data, with special attention to cardiovascular-related information and PE-related obstetric history (previous PE, fetal growth restriction, abruptio placentae or stillbirth) prior to the examination.

## Outcome measures

### Primary outcome

Maternal cardiac dysfunction or remodeling in the first and third trimesters of pregnancy and 12 months postpartum, defined as any of the following:Abnormal cardiac performance in echocardiographic assessments.Abnormal concentrations of cardiac biomarkers (Copeptin, hs-cTnT, NT-proBNP).

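### The primary analysis compares groups at each visit without using the 11-13 week assessment as a baseline, so abnormality present at entry cannot be separated from later change

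*Protocol article*

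**What the plan says.** - **Outcome.** The Primary outcome section reads "Maternal cardiac dysfunction or remodeling in the first and third trimesters of pregnancy and 12 months postpartum, defined as any of the following", followed by two components: abnormal echocardiographic performance, or abnormal copeptin, hs-cTnT or NT-proBNP.
- **Analysis.** Under Database development and statistical analysis, the groups are compared on all recorded variables at each of the three evaluation points by ANOVA with post-hoc tests, or by Chi-squared tests for proportions. Confounders are to be explored with logistic regression; none is named. Measurements are normalised for gestational age.
- **First assessment.** Under Procedures and interventions, after screening at 11-13+6 weeks and consent, "a maternal echocardiographic evaluation will be performed, and blood and urine samples will be obtained". There is no pre-pregnancy measurement.
- **Exclusions.** The list is open: "Pregnancies with previous maternal conditions such as thrombophilia, type-1 diabetes, hyperthyroidism, any renal disease, severe maternal illness", then certain infections, "previous venous or arterial thrombotic events" and other items. Heart disease and chronic hypertension are not named.
- **Groups.** Inclusion criteria: 280 high-risk women, selected by a screen that includes blood pressure and maternal risk factors; 100 healthy low-risk controls; 60 women enrolled when PE is diagnosed.
- **Background.** On abnormal cardiovascular adaptation in PE, the article says "which occurs more frequently if there is a hypertensive disorder before pregnancy".
- **Aim.** Whether a "relationship exists between angiogenic environment during pregnancy and the risk of maternal cardiovascular dysfunction and remodeling".

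**The concern.** The Discussion proposes a sequence: an anti-angiogenic profile early in pregnancy leads to cardiac remodeling, which promotes PE and injury that may persist. Examining that sequence requires telling a woman's state at entry from what develops afterwards. The visits allow this for everyone enrolled in the first trimester, but the stated analysis does not use it. A group difference at 28-32 weeks or at 12 months may therefore be new, or may be the entry difference seen again.

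If pre-existing abnormality were equally common in all groups, this would mainly add noise. Here the entry rules select toward raised blood pressure in one group and away from it in the other, and the article itself links prior hypertension to abnormal adaptation. The carried-over difference is then expected to run in the direction of the study hypothesis.

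**Working it through.** **1. The plan's own figures.** 40 true PE + 240 false PE = 280 high-risk. 280 + 100 = 380 first-trimester enrollees. 380 + 60 = 440, which matches the stated total. The article gives no event rate, effect size or power, so there is no further figure to reproduce.

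**2. Who has a baseline.** The 380 first-trimester enrollees are scheduled for a study echocardiogram and blood sample at 11-13 weeks. The 60 established-PE women enter at diagnosis and have neither.

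**3. What the stated analysis does with that baseline.** ANOVA and Chi-squared tests at each visit use only that visit's values. Gestational-age normalisation removes the expected effect of gestation, not a woman's own prior abnormality. The logistic regression names neither the first-trimester value nor prior hypertension.

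**4. Size, on assumptions.** None of these inputs is in the documents:
- 5-15% of high-risk women have prior hypertension: 280 × 0.05 = 14; 280 × 0.15 = 42.
- 30-50% of those show an abnormality that predates any pregnancy effect: 14 × 0.30 = 4.2; 42 × 0.50 = 21.
- As a share of the high-risk group, q = 4.2/280 = 1.5% to 21/280 = 7.5%.
- Controls: q = 0. Background abnormality from other causes: 10% in both groups. No pregnancy effect. The pre-existing abnormality persists to the visit analysed.

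Outcome rates: controls p₁ = 0.10; high-risk p₂ = q + (1 − q) × 0.10.
- q = 1.5%: p₂ = 0.015 + 0.985 × 0.10 = 0.1135, difference d = 0.0135.
- q = 7.5%: p₂ = 0.075 + 0.925 × 0.10 = 0.1675, difference d = 0.0675.

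Chance of p < 0.05 (two-sided, 100 v 280, normal approximation): Φ[(d − 1.96·SE₀)/SE₁] plus the opposite tail, where SE₀ = √[p̄(1−p̄)(1/100 + 1/280)], SE₁ = √[p₁(1−p₁)/100 + p₂(1−p₂)/280] and p̄ is the pooled rate.

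| q in high-risk | p₁ v p₂ | SE₀ | SE₁ | Chance of p < 0.05 |
|---|---|---|---|---|
| 1.5% | 0.100 v 0.1135 | 0.0364 | 0.0355 | 0.051 + 0.008 = 0.06 |
| 5% | 0.100 v 0.145 | 0.0396 | 0.0366 | 0.19 |
| 7.5% | 0.100 v 0.1675 | 0.0416 | 0.0374 | 0.35 |

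With no pre-existing difference the figure would be 0.05. Larger values need inputs outside the assumed range: q = 10% gives 0.55 and q = 20% gives 0.98. Allowing 2% pre-existing abnormality in controls lowers the 10% case from 0.55 to 0.36.

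**The case against.** Several stronger readings are tempting, and the article does not support them.

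- **That the plan treats old disease as an effect of the angiogenic environment.** The primary aim is a relationship, and the Discussion says the study assesses associations and leaves causal links to further work. The directional language there is not an analysis rule.
- **That prior heart disease is not excluded.** The exclusion list is open-ended and names severe maternal illness and previous arterial thrombotic events, so some heart disease is already kept out. Only non-severe heart disease and chronic hypertension are left without a named exclusion.
- **That a woman abnormal at 11-13 weeks and unchanged later is necessarily one pooled event.** The any-of wording covers the two components, and the analysis section compares groups visit by visit. First-trimester abnormality is therefore visible at its own visit.
- **That the outcome should become new abnormality only.** Early remodeling is the proposed step before PE, and first-trimester markers are a stated secondary aim. Replacing the outcome would discard that question and remove the 60 established-PE women from the primary outcome.

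It can also be said that cardiovascular history is collected, that confounders will be explored, and that a covariate list is commonly left to an analysis plan. That is fair for the list as such. It does not cover the stated primary comparison, which is unadjusted and, followed as written, carries entry differences into both later visits. Finally, abnormality unrelated to the angiogenic profile distorts the group contrast but is mainly noise in within-group biomarker correlations. That limits the reach of the point without removing it.

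**Conclusion.** The point holds in a limited form. The visit-by-visit group comparison cannot separate abnormality present at entry from later change, and the selection of the groups makes an entry difference likely. The first-trimester outcome is legitimate and should stay; what is missing is its use as a baseline for the later visits.

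The size is uncertain. On the assumptions shown, the chance of a significant high-risk versus control difference without any pregnancy effect runs from about 0.06, barely above nominal, to 0.35. Every input to that range except the group sizes is assumed, including zero pre-existing abnormality in controls, so it illustrates the mechanism and does not estimate the bias in this cohort. This is a worthwhile, low-cost improvement to the analysis, not a flaw that invalidates the design.

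**What to change.** 1. Keep the first-trimester outcome as stated and report it as prevalence at entry, by group.
2. For the 380 first-trimester enrollees, analyse the third-trimester and 12-month outcomes adjusted for the first-trimester value: ANCOVA for continuous measures, logistic regression for abnormal/normal. As a supporting analysis, report new abnormality among women who were normal at entry.
3. Include pre-pregnancy hypertension, available from the Data collection questionnaire, as a fixed covariate. Add a sensitivity analysis omitting these women and any with known pre-pregnancy heart disease.
4. Report the 60 established-PE women separately from the baseline-adjusted analysis, since they have no first-trimester study assessment. They remain in the stated comparisons at the visits they attend.

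Cost: a little more analysis and no new measurements. The adjusted analysis excludes the 60 established-PE women. It also addresses change after 11-13 weeks, so any remodeling completed before then appears only in the entry prevalence; the two results should be read together.
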